### Analysis populations – DILI strategy study

All patients in the DILI strategy study will be analysed according to their randomised arm as an intention-to-treat (ITT) analysis. The two primary comparisons are the comparisons of strategies 1 and 2, respectively, versus strategy 3 (with tests conducted at the unadjusted two-sided 5% significance level) and comparisons between strategies 1 and 2 will be exploratory only.

### Primary endpoint analysis – main trial

The primary endpoint of this trial is the time to death or a new neurological event during 12 months of follow-up. The primary endpoint will be analysed using a Cox proportional hazards regression model with treatment as the only covariate and stratification by TBM MRC severity grade at enrolment (I, II, or III) and LTA4H genotype (CC or CT). The primary effect measure is the resulting hazard ratio comparing dexamethasone vs. placebo with a corresponding confidence interval and p-value. Non-inferiority of placebo in the entire population or the CC-genotype subgroup will be established if the corresponding test (at the one-sided 2% or 0.87% significance level for the full population and the CC subgroup, respectively) rejects the null hypothesis that dexamethasone decreases the hazard of the primary endpoint by 25% or more. Superiority of placebo will additionally be established, if the null hypothesis that dexamethasone does not affect the hazard of the primary endpoint can be rejected against the one-sided alternative that dexamethasone causes harm. The distribution of the primary endpoint will also be visualized using Kaplan-Meier plots and explicit survival estimates at 3, 6, 9, and 12 months of follow-up will also be calculated.

The proportional hazards assumption will be formally tested based on scaled Schoenfeld residuals and visually assessed by a plot of the scaled Schoenfeld residuals versus transformed time. In case of a significant test, a formal comparison of the absolute risk of an event by 12 months between the two groups will also be performed (using a Wald-type test based on Kaplan-Meier estimates at 12 months and associated standard errors using Greenwood’s formula). The homogeneity of the treatment effect on the primary endpoint across subgroups will be assessed by subgroup analyses and formal tests of interactions between treatment and the following grouping variables: genotype (CC or CT), TBM MRC severity grade at enrolment (I, II, or III), and drug resistance pattern (MDR-TB or rifampicin mono-resistance, isoniazid resistant non-MDR, no or other resistance). To obtain an adjusted treatment effect estimate and to assess the effect of other covariates, the primary endpoint will also be modelled using a multivariable Cox proportional hazards regression model including the following covariates (in addition to the treatment group): genotype, TBM MRC severity grade at enrolment, and drug resistance pattern.

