### Design and setting

LAST ACT is a parallel group, randomised (1:1), double blind, placebo-controlled, multi-centre Phase III non-inferiority trial, comparing dexamethasone versus placebo for 6-8 weeks in addition to standard anti-tuberculosis treatment in HIV-uninfected patients with TBM stratified by LTA4H genotype.
** The trial will be set in two hospitals in Ho Chi Minh City, Vietnam. The trial will enrol approximately 720 HIV-uninfected adults (≥18 years) with a clinical diagnosis of TBM, as judged by the attending physician, requiring immediate anti-tuberculosis treatment. Amongst these, 640 participants with CT or CC- LTA4H genotype will be randomised to either dexamethasone or placebo. The remaining participants (approximately 80) with TT-genotype will be treated with standard-of-care dexamethasone. The trial schema is shown in
Figure 1.

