#### Randomisation

Once a participant or their relative has provided written informed consent to enter the study, 5mls of blood will be taken for rapid LTA4H genotyping. The blood will be transported immediately to the OUCRU laboratory within HTD where daily LTA4H genotyping (except at weekends) will be performed. Randomisation will occur once the result of the LTA4H genotyping is available. LTA4H CC- and CT-genotype participants will be randomised to two parallel groups in a 1:1 ratio, receiving either dexamethasone or placebo for 6–8 weeks (according to disease severity). TT-genotype participants will be treated with open-label dexamethasone for 6-8 weeks (according to disease severity). All patients will receive standard anti-tuberculosis chemotherapy. Randomisation will be stratified by participating hospital/site, LTA4H genotype (CC or CT), and modified MRC disease severity grade (
Supplementary File 1) assessed on day 0 when consent is given.

The randomisation list will be computer-generated based on random permuted blocks with variable block size following Oxford University Clinical Research Unit (OUCRU) standard operating procedures. The OUCRU biostatistician in charge of randomisation list preparation will set up statistical code to generate the randomisation list and transfer it to the Study Pharmacist. The Study Pharmacist will then change the random seed, i.e. the initialisation of the random numbers generator, in the statistical code in order to blind the biostatistician and then run the code to prepare the final randomisation list. The generated randomisation lists will be securely incorporated within the trial database. A reliable manual back-up system will also be available. Randomisation to the three strategies for DILI will be 1:1:1 with stratification by initial randomisation (dexamethasone or placebo).

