### Primary endpoint analysis – DILI strategy study

For the analysis of the primary endpoint of the DILI strategy study, the non-parametric Wilcoxon rank sum test will be used for pairwise comparisons. An additional adjusted analysis (with adjustment for the initial randomisation, HIV-status, and the time from initial randomisation to the second randomisation) will be also be performed treating the outcome as an ordinal outcome and using a proportional odds logistic regression model (which can be interpreted as an extension of the Wilcoxon rank sum test).

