### Secondary endpoint analysis

Overall survival will be analysed in the same way as the primary endpoint (except that non-inferiority will not be formally assessed). Neurological disability (as assessed by the ordinal modified Rankin scale) at 12 months will be compared between the two arms with a proportional odds logistic regression model with the treatment assignment as the main covariate and adjustment for genotype and TBM MRC severity grade. The result will be summarised as a cumulative odds ratio with a corresponding 95% confidence interval and p‐value. Patients with a missing 12 month disability assessment will be excluded from the main analysis but an alternative analysis based on multiple imputation (including disability assessments at earlier time points in the imputation model) will also be performed. The number and proportion of subjects requiring ‘rescue’ corticosteroids will be summarised by treatment arm. Comparisons will be based on logistic regression with the treatment assignment as the main covariate and adjustment for genotype and TBM MRC severity grade.

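### Hospital is a randomisation stratum but is missing, without a stated reason, from every main-trial efficacy model; adding it is a free improvement of minor weight

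*Protocol article*

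**What the plan says.** The Randomisation section names three factors for the main trial: "Randomisation will be stratified by participating hospital/site, LTA4H genotype (CC or CT), and modified MRC disease severity grade". The Design and setting section says how many hospitals there are: "The trial will be set in two hospitals in Ho Chi Minh City, Vietnam".

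The analysis sections use two of the three factors:

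- **Primary endpoint:** a Cox model in which treatment is the sole covariate, using "stratification by TBM MRC severity grade at enrolment (I, II, or III) and LTA4H genotype (CC or CT".
- **Overall survival:** analysed in the same way, apart from the non-inferiority test, so it inherits the same strata.
- **Multivariable Cox model:** besides treatment, the covariates are "genotype, TBM MRC severity grade at enrolment, and drug resistance pattern".
- **Rankin score and rescue corticosteroids:** regression models with "adjustment for genotype and TBM MRC severity grade".

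Hospital appears in none of these, and no reason is given. By contrast, the section on analysis populations explains at some length why the second (DILI) randomisation is ignored in the primary analysis.

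**The concern.** The usual principle is to analyse by the factors used to balance the allocation. Stratified allocation removes some chance variation between arms. A model that omits a prognostic stratification factor does not credit that removal, so its standard error is too large. In a Cox model the omission also changes the estimand: the hazard ratio becomes an average over hospitals, which lies closer to 1 than the hazard ratio within hospital.

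Both effects touch confirmatory tests. The plan tests non-inferiority of placebo against a hazard ratio (dexamethasone versus placebo) of 0.75 and may then claim superiority of placebo. Movement towards 1 is movement away from the 0.75 margin. An inflated standard error makes it harder to claim superiority, and the sample size section says that some evidence of harm is needed before dexamethasone would be given by genotype.

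This is not a matter left open for an analysis plan, because the protocol states the strata of the confirmatory model exactly.

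**Working it through.** **Inputs from the protocol.** Margin 0.75; assumed true hazard ratio 1.15; one-sided 2% for the full population; 80% power; 35% 12-month risk on dexamethasone; overall risk at least 32%; 11% inflation; 640 randomised 1:1.

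**The plan's own figures.** Events = 4(z₀.₉₈ + z₀.₈₀)² / [ln(1.15/0.75)]² = 4(2.054 + 0.842)² / 0.4274² = 183.5, that is 184 as stated. Patients = 184/0.32 × 1.11 = 638, stated as 640. The formula does not use the strata, so neither figure changes if hospital is added.

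**Simulation of the omission.** 6,000 trials per scenario, 640 patients each, permuted blocks within hospital × genotype × MRC grade, and 35% risk on dexamethasone. Each trial was analysed by a Cox model stratified by grade and genotype, without and then with hospital as a further stratum. The following are assumptions, not protocol figures: hospital hazard ratio 1 to 3; hospital shares 50:50 (25:75 was similar); MRC mix 35/40/25% with relative hazards 0.5/1/2.2; 53% CT; constant hazards; no loss to follow-up.

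*At the margin (true hazard ratio 0.75):*

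| Hospital HR | Estimate without / with hospital | Model SE / actual SE, without hospital | Type I error without / with hospital (nominal 2%) |
|---|---|---|---|
| 1 | 0.750 / 0.750 | 0.1279 / 0.1280 | 1.9% / 1.9% |
| 1.5 | 0.752 / 0.750 | 0.1279 / 0.1257 | 2.1% / 2.1% |
| 2 | 0.759 / 0.752 | 0.1281 / 0.1247 | 2.3% / 2.1% |
| 3 | 0.766 / 0.749 | 0.1282 / 0.1222 | 2.4% / 2.2% |

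The standard error is overstated by 0.1279/0.1257 − 1 = 1.8%, 0.1281/0.1247 − 1 = 2.7% and 0.1282/0.1222 − 1 = 4.9% at hospital hazard ratios of 1.5, 2 and 3. The Monte Carlo error of each type I error is √(0.02 × 0.98/6000), about 0.2 percentage points.

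**Why the net effect is small.** Take a hospital hazard ratio of 2. The shift is ln(0.7589/0.75) = 0.0118, or 0.0118/0.1281 = 0.09 standard errors. By itself it would raise the error rate from 2.0% to P(Z > 2.054 − 0.092) = 2.5%. The inflated standard error works the other way: the test statistic has standard deviation 0.1247/0.1281 = 0.973, so together they give P(Z > 1.962/0.973) = 2.2%. The simulated 2.3% agrees within its error.

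*At the design alternative (true hazard ratio 1.15):*

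| Hospital HR | Non-inferiority power without / with hospital | Superiority power without / with hospital |
|---|---|---|
| 1 | 85.8% / 85.4% | 14.9% / 14.8% |
| 1.5 | 85.1% / 85.2% | 14.4% / 14.7% |
| 2 | 84.8% / 84.8% | 13.5% / 15.1% |
| 3 | 85.9% / 85.9% | 11.9% / 14.9% |

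Non-inferiority power exceeds the planned 80% because the simulated trials have about 213 events, not 184.

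*With no treatment effect (true hazard ratio 1):* the superiority test without hospital rejects in 1.7%, 1.9%, 1.7% and 1.3% of trials at hospital hazard ratios of 1, 1.5, 2 and 3. With Monte Carlo error of about 0.2 points, it is clearly conservative only at 3.

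The CC co-primary population, tested at 0.87% with about half the events, was not simulated.

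**The case against.** **The premise is not documented.** All of the consequences require hospital to predict outcome after grade and genotype. The protocol gives no outcome by hospital and does not say that the two hospitals differ in case mix. A hospital effect is plausible: the imaging, hyponatraemia and adrenal sub-studies run at one hospital only, and the endpoint includes clinically detected neurological events. Plausible is not shown, and with a hospital hazard ratio of 1 nothing happens. This objection stands, so the consequence has to be stated conditionally.

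**A reader might infer that the omission biases the trial towards declaring non-inferiority.** The documents do not support that. Stratified allocation balances hospital between arms, so there is no confounding. The shift is non-collapsibility: an average over hospitals is estimated in place of a within-hospital value, and the margin is itself translated into an overall risk difference. The larger standard error offsets part of the shift, and the type I error with and without hospital differs by about one Monte Carlo standard error at most.

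**A reader might also extend the point to the DILI study**, where "Randomisation to the three strategies for DILI will be 1:1:1 with stratification by initial randomisation (dexamethasone or placebo" is followed by a primary analysis in which "the non-parametric Wilcoxon rank sum test will be used for pairwise comparisons". That does not carry over. The same section plans an additional proportional odds analysis adjusted for the initial randomisation, HIV status and time between randomisations, and the DILI sample size was simulated with the Wilcoxon test. A stratified rank test as primary would be a preference.

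What survives is that hospital is a design factor, the confirmatory model drops it, and no reason is given.

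**Conclusion.** The point holds as a minor mismatch between design and analysis. The omission itself is certain from the text. Its effect is conditional on hospital being prognostic given MRC grade and genotype, and the sizes rest on assumed hospital hazard ratios and the simulation settings above.

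In that case the main cost is efficiency: a standard error about 2% to 3% too large at the margin for a hospital hazard ratio of 1.5 to 2 (about 5% at 3), and a small loss of superiority power, 1.6 percentage points at 2 and 3.0 at 3. The hazard ratio at the margin moves by about 0.002 to 0.009 for a hospital hazard ratio of 1.5 to 2, and by 0.016 at 3. The non-inferiority conclusion, the event target and the sample size are not put at risk in the full population. Calling the primary analysis invalid or anti-conservative would go beyond what these figures show.

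**What to change.** In the primary endpoint analysis, stratify the Cox model by hospital as well as MRC grade and genotype: 2 × 3 × 2 = 12 strata in the full population and 2 × 3 = 6 in the CC population. Apply the same strata to overall survival. Add hospital as a covariate in the multivariable Cox model and in the Rankin and rescue-corticosteroid models. If the sponsor prefers to keep hospital out, state why and prespecify the hospital-stratified model as a sensitivity analysis.

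The cost is a line or two of wording. Hospital is known for every patient because allocation uses it. If hospital has no effect, simulated non-inferiority power in the full population is 85.4% with hospital against 85.8% without, a difference within simulation error. The same check should be run for the smaller CC population before the wording is fixed.

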### Clinical assessment

Clinical assessment will include conscious level by GCS, new or ongoing focal neurological deficit, clinical treatment response, all serious adverse events, all adverse events of any grade leading to modification of anti-tuberculosis treatment or its interruption/early discontinuation (and clinician-assessed likelihood of relationship of adverse event to dexamethasone), and adherence to drugs (study drug and anti-tuberculosis drugs). Assessment of disability by the modified Rankin scale will be performed at day 30 from randomisation, monthly until completion of anti-TB drugs, and at month 12.

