We set the non-inferiority margin in favour of dexamethasone at a hazard ratio (HR) of 0.75 and assume a true HR of 1.15 in the CC/CT population. Assuming an absolute risk of a neurological event or death in the dexamethasone group by 12 months of 35%, a HR=1.15 corresponds to risk of 31.2% on placebo, and the non-inferiority margin implies that we can exclude an absolute risk increase of placebo of (at worst) +8.7%. Under these assumptions a total of 184 neurological events or deaths would be required to obtain 80% power at the one-sided 2% significance level. Assuming an overall event risk of ≥32%, and an 11% sample size increase to compensate for loss-to-follow-up and reductions in power due to the allowance for stopping due to futility, a total of 640 HIV-negative subjects with CC or CT-genotype will be randomised into the trial. Based on experience from our earlier TBM trials
^4,
7,
18,
19^, only a very low number of subjects will be excluded from the per-protocol population, hence only minimally reducing power in this population. Of note, with 184 neurological events or deaths (half of them in the CC group), the trial also has 80% power to prove harm of dexamethasone in the CC/CT group or the CC group in case the true HR is at least 1.54 in all subjects or 1.96 in CC patients, respectively. Our recent trial enrolled 468 HIV-uninfected adults with TBM in 30 months and 90% of them had CC or CT-genotype. Assuming similar recruitment rates, enrolment will be complete within 4 years.

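### The adjusted Cox, disability and rescue-corticosteroid models measure baseline severity only by the day-0 MRC grade, although GCS at randomisation is already recorded; adding it would be a modest gain in efficiency.

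*Protocol article*

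**What the plan says.** All references are to the protocol article.

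- **Primary endpoint analysis – main trial.** The deciding analysis is a Cox model "with treatment as the only covariate and stratification by TBM MRC severity grade at enrolment" and by LTA4H genotype. A further multivariable Cox model, intended to give an adjusted treatment effect and to estimate the effects of other covariates, is fitted "including the following covariates (in addition to the treatment group): genotype, TBM MRC severity grade at enrolment, and drug resistance pattern".
- **Secondary endpoint analysis.** Overall survival follows the primary analysis, without a formal non-inferiority assessment. The Rankin and rescue-corticosteroid models are each fitted "with the treatment assignment as the main covariate and adjustment for genotype and TBM MRC severity grade".
- **Randomisation.** The MRC grade used for stratification is "assessed on day 0 when consent is given". Randomisation waits for the genotype result, which the Inclusion criteria section does not expect to take more than 3 days.
- **Clinical assessment.** "Clinical assessment will include conscious level by GCS". Table 3 schedules a clinical assessment at randomisation. The Inpatient assessment section adds daily GCS in hospital and a research visit at randomisation.

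No main-trial model lists GCS as a covariate.

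**The concern.** Two of the three covariates in the multivariable Cox model, genotype and MRC grade, are already strata of the primary model. Drug resistance pattern is the only new one. As a check on chance imbalance in severity the model can therefore hardly differ from the primary result.

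The grade has three levels and may be a few days old at time zero. GCS at randomisation is finer and more recent, and a sustained fall in GCS is itself part of the primary endpoint. If GCS carries prognostic information within an MRC grade, leaving it out of a proportional odds or Cox model moves the estimated effect towards 1 and costs power when a real effect exists. Disability is the comparison most exposed: the Primary aim section names it among the outcomes on which placebo is to be judged, and its model has no severity term beyond the grade.

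**Working it through.** **1. Reproduce the design, to check that the setting is understood.** The plan states: "We set the non-inferiority margin in favour of dexamethasone at a hazard ratio (HR) of 0.75". It goes on to "assume a true HR of 1.15 in the CC/CT population", and says that "a total of 184 neurological events or deaths would be required to obtain 80% power at the one-sided 2% significance level".

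- Events = 4(z₀.₉₈ + z₀.₈₀)² / [ln(1.15/0.75)]² = 4(2.054 + 0.842)² / 0.4274² = 183.5, rounded up to 184. This agrees.
- N = 184 / 0.32 × 1.11 = 638, against 640 stated. This agrees.
- Risk on placebo at the margin = 1 − 0.65^(1/0.75) = 43.7%, which is 8.7 points above 35%. This agrees, and it needs no GCS term.

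**2. Assumptions for what follows.** The documents do not say how strongly GCS predicts outcome within an MRC grade. It is represented by a standard normal score with an assumed log odds ratio or log hazard ratio per SD. Grade shares of 35/42/23% are also assumed. For the Cox runs, 12-month risks by grade of 20/35/55% were scaled to 32% overall, with 5% random censoring.

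**3. Rankin comparison.** Proportional odds model, seven levels, N = 600, true conditional odds ratio about 1.57, two-sided 5%, 2,000 trials per row (Monte Carlo standard error about 1 point).

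| Assumed log-OR per SD | Power without | Power with | Gain | Estimated OR without / with |
|---|---|---|---|---|
| 0.4 | 82.3% | 84.2% | 1.9 points | 1.54 / 1.56 |
| 0.8 | 76.0% | 83.4% | 7.4 points | 1.49 / 1.56 |
| 1.2 | 66.9% | 82.6% | 15.7 points | 1.43 / 1.57 |

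The rescue and overall survival models were not simulated. The same mechanism applies, but no size is claimed for them.

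**4. Chance imbalance.** With 320 per arm, the difference in mean score between arms has a standard error of √(1/320 + 1/320) = 0.079 SD. To first order, an imbalance of one standard error shifts the unadjusted log effect by 0.079 × 0.4 = 0.03, or by 0.079 × 0.8 = 0.06. As a ratio this is about 3% to 6%.

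**5. Cox model, for direction and size.** N = 640, about 200 events, stratified by MRC grade. Severity log hazard ratio per SD is 0.4 / 0.8.

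| True conditional HR | Mean estimate without the covariate | Non-inferiority declared, without | Non-inferiority declared, with |
|---|---|---|---|
| 0.75 | 0.756 / 0.776 | 2.3% / 3.4% | 2.0% / 2.0% |
| 1.15 | 1.146 / 1.132 | 82.6% / 80.3% | 83.2% / 83.3% |

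At a true HR of 1.0 there is no shift. Below 1 the estimate moves up, away from the margin. Above 1, where the design places the truth, it moves down towards the margin. With a weak covariate (0.2 per SD) the limiting value at 0.75 is only 0.755.

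**The case against.** **A reader might infer that the omission pulls the trial towards non-inferiority.** The documents do not support this. The pull in that direction exists only if dexamethasone truly helps. At the design HR of 1.15 it works against non-inferiority, by about 1 to 3 points of power.

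**A reader might also infer that the primary error rate rises above 2%, to as much as 3.4%.** That figure appears only if 0.75 is read as a hazard ratio conditional on GCS. The null hypothesis belongs to the stratified primary model, and the margin is tied to group-level 12-month risks. A GCS-conditional HR of 0.75 corresponds to about 0.76 to 0.78 in that model, which lies outside its null, so rejecting is not an error. This is non-collapsibility, a change of estimand rather than bias, and the primary test keeps its level for its own estimand.

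Other points on this side:

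- The multivariable Cox model is not redundant. A stratified Cox model gives no estimates for genotype or MRC grade, and this one does. That stands, but it does not make the model a fuller adjustment for severity.
- The MRC definition is in a supplementary file that is not shown, so its overlap with GCS cannot be checked. That stands: the gain may be as small as 2 points.
- Adjusting for the stratification factors is a valid choice, and an SAP may add covariates. The choice is valid, but the article states these covariate lists explicitly, so the point concerns what is written.
- Putting GCS into overall survival but not into the primary model would make the two hazard ratios condition on different things. That stands, and it is why the survival adjustment should be supportive only.

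**Conclusion.** The point holds as a modest improvement to the adjusted and secondary analyses. The covariate lists contain no severity measure beyond a three-level grade fixed up to about 3 days before time zero, while a finer and more recent one is already collected. For the Rankin comparison the gain is about 2, 7 or 16 points of power at an assumed log odds ratio of 0.4, 0.8 or 1.2 per SD. There is also some protection against chance imbalance at randomisation. These sizes rest on an assumed prognostic strength and an assumed treatment effect, neither of which the documents give. Since the Rankin, rescue and adjusted Cox analyses carry no non-inferiority margin, the estimand problem does not arise there. Nothing here shows a fault in the primary test, its margin or its sample size.

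**What to change.** Before unblinding, pre-specify GCS at randomisation as a continuous covariate, beside MRC grade and genotype, in:

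- the multivariable Cox model for the primary endpoint, keeping drug resistance pattern;
- the proportional odds model for 12-month Rankin score;
- the logistic model for rescue corticosteroids;
- a supportive adjusted model for overall survival, next to the planned one.

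State that the value is the one recorded at the randomisation visit, before the first dose of study drug. Leave the primary stratified Cox model and its 0.75 margin unchanged.

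The cost is a sentence or two in the analysis section and no new data. The small downside is that the adjusted estimates become conditional on GCS and should be labelled so. Choosing the covariate after unblinding would forfeit its credibility, so the timing matters more than the wording.
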